
### Familiarisation sessions

Participants will be asked to wear light clothes in which it is comfortable to perform exercise, and be given a thorough demonstration of all balance and strength tests, which they will then attempt.

Balance tests will assess postural sway with the participants’ eyes open and closed with them standing as still as possible on a force-measuring platform (AccuGait, AMTI, Watertown, MA, USA) with their feet side-by-side and heels 15 cm apart for 40 s, or feet together for 60 s. Participants will then practice the standard Y-balance test of single-leg balance [31], involving pushing their non-standing leg as far as they can forward, behind and to the right, and behind and to the left, whilst maintaining balance on the standing leg.

Leg strength assessments will be conducted on a pneumatic leg press machine (A420, Keiser®, Fresno, CA, USA), instrumented to measure the force applied to the foot pedals with the velocity the pedals moved at 400 Hz. Following a standardised warm-up, participants will complete one repetition maximum (1RM) tests on the leg press for single repetitions up to the greatest resistance at which one repetition can be completed, with self-selected rest and increments in force between repetitions. Determination of 1RM is commonly used in adult populations [32–34] and is considered safe [35], valid and reproducible [36] in older populations. Following a recovery period of at least 5 min, the participants will then practice the incremental power test on the leg press that will be used in the main trials. In this test, participants will complete approximately 10 discrete repetitions of the leg press exercise, with the movement in each repetition performed as quickly as possible. The resistance will increase in each successive repetition, starting with very low resistance up to approximately the previously achieved 1RM, with increasing recovery periods between repetitions. Participants will then be asked to repeat a similar familiarisation and 1RM test on a pneumatic knee extension machine.

Finally, participants’ ability to generate their maximum possible force (i.e. neural drive) will be examined by maximal voluntary isometric calf muscle contractions, with concomitant surface-evoked twitch stimulation to produce maximal stimulated force. The participant will be seated on a custom-built device, with the ankle dorsi-flexed to 10° and the knee braced at 90° against a strain gauge to measure the force of isometric contraction of the plantar-flexor muscles. Stimulating electrodes will be attached to the skin surface of the calf muscle region, with the cathode and anode placed on the upper and lower thirds of the triceps surae respectively. Stimulation will be delivered with a DS7 stimulator (Digitimer, Letchworth Garden City, UK). Initially, the force of a maximum voluntary plantar-flexor contraction will then be obtained, followed by a maximum evoked from single twitches at rest. Thereafter, the participant will make three repeated attempts to match the previously obtained maximum voluntary force with a pulse of electrical stimulation (of the same voltage previously identified to evoke maximal twitch force) passed across the calf muscle to maximally stimulate the muscle at the point of maximum force. The difference between the maximum voluntary force and maximum twitch-evoked force will indicate the participant’s ability to maximally stimulate their muscle [37].

### Main trials

The main trials will take place the day before the 14-day step-reduction (day 0) and the day after (day 15) (see Fig. 1). See Fig. 2 for schematic overview of the main trial day timeline.

**Fig. 2 Fig2:**
[figure not shown]
A schematic overview of the main trial data collection day; arrows indicate the timing of blood,adipose and muscle samples

Participants will be asked to report to the laboratory after a 10-hour overnight fast, wearing lightweight clothing with no metal components. Balance scales and a stadiometer will be used to determine the participant’s weight and height for calculation of BMI. A whole body dual-energy X-ray absorptiometry scan (DXA (Discovery; Hologic, Bedford, UK)) and a peripheral quantitative computed tomography scan ((pQCT) (XCT 3000 scanner; Stratec, Pforzheim, Germany)) of the calf (66 % tibia length) and thigh (25 and 50 % femur length) will be performed. An ultrasound scan of the medial gastrocnemius and vastus lateralis muscles will be conducted whilst standing to examine fascicle length and pennation angle (Echoblaster 128EXT-1Z, Revision C, and LV7.5/60/96z Transducer, LS128 CEXT, both TELEMED, Vilnius, Lithuania). The pQCT and ultrasound will be taken from the dominant leg. Subsequently, participants will complete five self-paced walks of 5 m whilst being filmed at 200 Hz with one camera in the sagittal plane to assess lower limb gait coordination.

A resting venous blood sample via cannula, followed by a biopsy sample of subcutaneous adipose tissue by needle aspiration, from approximately 5 cm lateral to the umbilicus, will be obtained after 15 min of seated/supine rest. Participants will then ingest a 200-ml dose of D_2_O water and undertake a mixed-meal tolerance test (mixed-macronutrient liquid meal of 2 g/kg BM carbohydrate; 0.8 g/kg BM fat; 0.4 g/kg BM protein) with 5-ml blood samples taken 15, 30, 45, 60, 90, 120, 150 and 180 min after consumption of the drink. Thereafter, a muscle biopsy will be sampled using the Bergstrom needle biopsy technique adapted for use with suction [38] from the vastus lateralis muscle. Consecutive muscle biopsies will be taken proximal to the previous biopsy site [39].

Participants will then undertake the balance testing as performed in the familiarisation procedure. The standard leg pressing warm-up will then be performed using the previously obtained 1RM, and the incremental power test as a measure of leg power will be undertaken. Following 2 min of recovery, participants will complete the assessment of neural drive of the calf muscle, followed by three sets of eight repetitions at 70 % 1RM on the leg press and leg extension (total of 48 repetitions). There will be 2 min of recovery between sets. Blood samples will be taken immediately on completion of exercise, and a muscle biopsy obtained from the contralateral leg after 90 min of rest. Whilst the participant rests, they will be asked to complete two questionnaires (The Pittsburgh Sleep Quality Index [40] and the World Health Organisation Quality of Life-BREF (WHOQOL-BREF) [41]).

### Step-reduction intervention

For 14 days participants will be asked to restrict their daily step count to 1500 steps per day. A portable pedometer will be worn by participants at all times throughout the day (excluding sleep) to allow accurate monitoring and feedback of step count. Step count will be recorded each day by the participant in a provided log-book. The pedometer will also automatically record daily step count, and will reset at midnight. An advice sheet will be provided to suggest strategies to reduce daily stepping. Participants will also wear a BodyMedia armband for the first 7 days of step-reduction. They will be asked to record their dietary intake on the first, seventh and 13th days of the step-reduction intervention using a dietary record sheet. For the two visits to the laboratory during the step-reduction period, transport arrangements will be made to minimise walking for the participant for the sake of the visits (i.e. door-to-door transport, transport within the facility/campus by wheelchair).

### Further assessments

On the third day of the 14-day step-reduction (day 3), participants will be asked to return to the laboratory for a blood sample and resting muscle biopsy. Participants in the exercise snacking group (ES-group) will be asked to perform an exercise snack in the laboratory. This will be repeated on the eighth day of the 14-day step-reduction (day 8), and 100 ml D_2_O water will be ingested.

Three days after the 14-day step-reduction (day 18), participants will be asked to return to the laboratory for a final resting blood sample and muscle biopsy to be taken.

### Exercise interventions

#### Pre-training group (PT)

The PT-group will attend 10 resistance training sessions across 4 weeks prior to the 14-day step-reduction, with sessions separated by at least 48 hours arranged at the participant’s convenience. The last training session will take place at least 3 but less than 7 days before the first main trial prior to step-reduction. All exercise sessions will be fully supervised by a member of the research team. Participants will complete the standardised warm-up on the Keiser leg press as performed during the familiarisation session. All training sessions will begin with leg press and leg extension, then alternate between two sessions (A and B) to incorporate variation into the programme (see Table 1). At the beginning of the fifth session, participants will repeat the 1RM and incremental power tests so exercise resistances can be adjusted to strength gains accordingly. Repetitions will be performed at a cadence of 1:1 for concentric-eccentric time, at a comfortable participant-selected pace that should be less than 5 s per complete repetition. Rest intervals between sets will be 90 to 120 s at the participant’s discretion.

**Table 1 Tab1:** Training session content and progression

Exercise		Sessions 1 and 2			Session 3–10		
Session A	Session B	Sets	Reps	Load	Sets	Reps	Load
Seated leg press		3	8	60 % 1RM	4	8	75 % 1RM
Seated leg extension							
DB calf raise	DB lat raise	2	10	70 % 10RM	3	10	80 % 10RM
DB bicep curl and press	RB seated row						

*1RM* maximum load at which a single repetition can be completed, *10RM* maximum load at which 10 repetitions can be completed, *DB* dumbbells, *Lat* lateral plane of motion, *RB* elastic resistance band, *Reps* repetitions

#### Exercise snacking regime

The exercise snacking requires only a stable kitchen chair to perform it, and no supervision is necessary. Participants will be asked to perform five exercises, each for 1 min followed by 1 min of rest. In that minute of exercise, the participant will perform as many controlled repetitions of the given exercise as possible. Participants will be asked to perform the exercise snacks three times daily at least 2 hours apart. The exercises are: sit-to-stand from a chair, seated alternating knee extension, standing alternating knee bends holding onto a chair, marching on the spot, and standing calf raises. Participants will always perform the sit-to-stand exercise first, and record the number of repetitions completed within 1 min, and thereafter participants may alternate the order of exercises, but will be asked to record the order in a log-book provided. Participants will be asked to record in the log book the number of steps taken immediately prior to, and after, each exercise snacking bout so as to not count the steps incurred for each exercise snack towards the 1500 steps/day limit.

#### Re-training

Participants will attend six resistance training sessions after the step-reduction, with the first training session taking place on the day of follow-up biopsy 3 once the sample has been taken. The remaining five sessions will take place over 14 days with sessions separated by at least 48 hours. These sessions will follow the same training regime as the PT-group undertook prior to commencing the step-reduction. Resistances for the exercises during re-training will be based on the data from the main trial post step-reduction.

#### Post re-training muscle size, strength and power assessments

Follow-up assessments of muscle function, balance, and muscle size and architecture will be made 2 days after the final session of the 2-week laboratory-based re-training. This assessment will include repetition of the DXA, pQCT and ultrasound scans, and the leg press incremental power test, test of neural drive, and standing balance.

### Acceptability and feasibility of adopting prescribed training regimes

Following the 2-week re-training period participants will be invited to take part in an interview to provide feedback on their experience during the trial to inform the feasibility assessment of each exercise regime. Participants will be provided with written information of the purpose of the interviews following their final re-training session, and reassured that participation is optional. Interviews will take place via telephone or in person according to participant preference, will be digitally recorded, transcribed verbatim and anonymised on completion. The interview schedule will include: (1) participants’ perceptions of the impact of inactivity on mood, appetite, vitality, sleep and other participant-generated concerns (for comparison across conditions), and (2) perceived barriers and facilitators and costs and benefits to adherence to the study protocol (i.e. if and how participants adapted the prescribed regimes, and factors they suggest would make the protocol easier to adopt).

### Sample processing and storage

Adipose and muscle tissue samples will be processed and analysed immediately on the day of collection or stored at −80 °C for later batch analysis. Blood collected into an ethylenediaminetetraacetic acid (EDTA) tube (2 ml) will be used to provide a full leukocyte differential and other standard haematology variables with an automated haematology analyser (SF-300, Sysmex Ltd., Milton Keynes, UK). Other blood samples collected into EDTA and plain tubes (5 ml) will be centrifuged to obtain plasma and serum, respectively. Blood collected into a sodium heparin tube (25 ml) will be used to isolate peripheral blood mononuclear cells. All samples will be stored at −80 °C for later batch analysis.

### Potential harms

An inherent risk associated with this study is the potential for loss in lean tissue and muscle function for participants; however, the graduated exercise re-training programme will aim to fully restore decrements in muscle size and function. Moreover, all exercise sessions and testing will be supervised by study staff with appropriate training. The blood and tissue sampling techniques used in the present study also carry a risk of discomfort to the participant; however, all study staff are fully trained, experienced, and adhere to best practice at all times to minimise this risk. All tissue sampling procedures will be performed in sterile conditions, and participants will be provided with extensive advice on aftercare of biopsy sites to minimise risk of infection. Any adverse events will be recorded, assessed, and monitored by the University of Bath sponsorship in the form of 6-monthly progress reports. All potential risks have been reported to, assessed, and approved by the study sponsor, Research Ethics Approval Committee for Health (University of Bath), and the Cornwall and Plymouth NHS Research Ethics Committee. Any modifications to the protocol will be approved by all aforementioned parties.

### Data analyses

#### Primary outcome measure

Differences in leg power from pre- to post-step-reduction intervention and differences between groups.

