### Study design

The methods described herein have been approved by the National Health Service (NHS) South West Cornwall and Plymouth Research Ethics Committee (REC) with an allocated REC reference number: 15/SW/0130. The project was subsequently registered as a clinical trial (ClinicalTrials.gov: NCT02495727). The Standard Protocol Items: Recommendations for Interventional Trials (SPIRIT) checklist was completed.

The study will address the objectives by way of a three-group randomised control trial. One group will act as a ‘control’ against which to compare the potential protective effects of exercise interventions insofar as this group will undertake step-reduction without either exercise intervention. Hypotheses: (1) reduced activity alone will result in loss of leg muscle power, (2) exercise pre-training will increase leg muscle power above baseline so any loss of muscle power due to the reduced activity period will be offset to such an extent that muscle power will remain above pre-training baseline, and (3) daily exercise snacking during the reduced activity period will attenuate the decline in leg muscle power due to reduced activity.

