### Population and sample size

Thirty healthy men (non-smokers without diabetes) aged 65–80 years will be recruited and randomised into three groups of 10 by way of minimisation to limit between group differences in mean age, BMI and habitual steps/day. Participant and researcher blinding to group allocation is not possible, and screening and group allocation will be implement by the same researcher for all participants

The study is powered to detect the protective effect of the aforementioned exercise strategies against loss of leg muscle power during 14 days of reduced activity. Over 14 days of step-reduction a mean (SD) decrease of 3.9 (2.4 %) in lower limb muscle mass is anticipated [15], with measures of muscle power expected to decline at a similar or faster rate; thus, seven participants per group (95 % power and 5 % alpha) will be required to observe changes in leg muscle strength. The decline in muscle power is expected to be the same in the pre-training group as in the control group, hence significant increases in leg muscle power prior to reducing physical activity are required. Significant increases in leg strength in older men with 4 weeks of pre-training could be observed using nine participants (95 % power and 5 % alpha) [30], and it expected that this would be equivalent in muscle power. It is difficult to predict the extent of the protective effect likely to be provided by the exercise snacking. Therefore, the sample size will be rounded to 10 participants per group to account for drop out and the potentially more subtle changes that might be observed in the secondary measures.

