## Discussion

This study aims to evaluate the effectiveness of two exercise strategies to attenuate the effects of 2 weeks of reduced activity on muscle power and other key health indices that are known to be affected by changes in physical activity level. Based on the previous studies, specifically implementing a daily step-reduction in older individuals [15, 21], it is expected that 14 days of reduced physical activity without protective interventions will have a significant physiological effect, with reductions in both muscle mass and insulin sensitivity. These changes, however, are reversible and participants will undergo re-training and assessments of muscle size and function will be made to ensure participants have returned to baseline (i.e. pre step-reduction). The step-reduction model and the exercise interventions incorporated into this study have been selected specifically because of their real-world applicability and high ecological validity. It is hoped that the exercise interventions will provide a proof of principle that even relatively modest exercise interventions may be effective countermeasures against reduced activity-induced muscle atrophy and decline in other health indices, and that these intervention can be further developed and optimised in future work. Given the limited previous literature using a reduced-activity model in older individuals it is hoped that inclusion of qualitative feasibility analysis may draw out questions of interest that may not have been previously considered, as well as considerations to improve future work in this field.

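### The stated primary outcome does not match hypothesis 2: the pre-training group's day-0 value already contains its training gain, so the expected difference from control in the day 0 to day 15 change is zero

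*Protocol article*

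**What the plan says.** - **Primary outcome** (Data analyses): "Differences in leg power from pre- to post-step-reduction intervention and differences between groups".
- **Timing** (Main trials): "The main trials will take place the day before the 14-day step-reduction (day 0) and the day after (day 15").
- **PT schedule** (Pre-training group): "The last training session will take place at least 3 but less than 7 days before the first main trial prior to step-reduction". The PT-group's day-0 value is therefore a post-training value.
- **Hypothesis 2** (Study design) uses a different reference point. After training and step-reduction, "muscle power will remain above pre-training baseline".
- **Planning assumption** (Population and sample size): "The decline in muscle power is expected to be the same in the pre-training group as in the control group". The same sentence continues: "hence significant increases in leg muscle power prior to reducing physical activity are required". The PT benefit is thus expected before day 0, not between day 0 and day 15.
- **Power test before training** (Familiarisation sessions): "the participants will then practice the incremental power test on the leg press that will be used in the main trials". It is described as practice.
- **Meaning of baseline** (Discussion): re-training is "to ensure participants have returned to baseline (i.e. pre step-reduction").

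**The concern.** The PT-group's benefit is planned to arise before day 0, but the primary outcome starts counting at day 0. A change score from day 0 subtracts the gain on which hypothesis 2 depends. If pre-training works as hypothesised, with a gain first and then the same loss as control, the primary between-group change for one of the two experimental arms has an expected value of zero. The test that would answer hypothesis 2, day-15 power against pre-training power, is not written into the outcome or the analysis.

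Hypothesis 1 (loss in control) and hypothesis 3 (exercise snacking, ES, attenuates the loss) are not affected, because day 0 is the right starting point for both.

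**Working it through.** **Inputs**
- Decline over step-reduction: x = 3.9%, SD 2.4% (Population and sample size). These are muscle-mass figures, and the plan expects power to fall at a similar or faster rate.
- Stated requirements at 95% power and 5% alpha: seven per group for the decline, nine for the training gain. Ten per group are planned.
- Training gain in power, G, and its SD: not given. A range is shown, in percentage points of pre-training power.

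**1. Reproduce the plan's figure.** Standardised decline = 3.9 / 2.4 = 1.625. A paired t test at two-sided 5% (sidedness assumed) has 94.4% power at n = 7 and 97.4% at n = 8. The stated seven is reproduced within rounding, so this calculation sizes a within-group decline. The nine for the gain cannot be reproduced without an effect and SD. As a two-sided paired test it would imply a standardised gain of about 1.38.

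**2. Day 0 to day 15 change, as stated.** Let pre-training power be P.
- Control: P at day 0, P − x at day 15; change −x.
- PT: P + G at day 0, P + G − x at day 15; change −x.
- PT minus control: (−x) − (−x) = (−3.9) − (−3.9) = **0** for every G.

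With a true difference of 0, a two-sided 5% test at 10 per group is significant 5% of the time, which is only the type I error.

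**3. Change from pre-training to day 15.** Assume control does not change before day 0.
- PT minus control: (G − x) − (−x) = **G**.
- Hypothesis 2 within PT: G − x > 0, that is G > 3.9.

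Two-sided power with 10 per group (SD 2.4 is the muscle-mass figure; 4.8 is double that, assumed):

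| G (assumed) | PT vs control, SD 2.4 | PT vs control, SD 4.8 | PT net change G − 3.9 | Within-PT test, SD 2.4 | Within-PT test, SD 4.8 |
|---|---|---|---|---|---|
| 3.9 | 93% | 41% | 0 | 5% | 5% |
| 5 | 99% | 60% | 1.1 | 25% | 10% |
| 8 | >99% | 94% | 4.1 | 99.7% | 67% |

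**4. Is a pre-training power value named anywhere as a baseline?** The incremental power test is done at familiarisation as practice, and again at the PT-group's fifth session to reset training loads. The primary outcome, the secondary outcomes and the Statistical analyses section name neither as a reference point. The Discussion equates baseline with the pre-step-reduction value.

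**The case against.** The strongest reply is that a reader might infer that hypothesis 2 cannot be answered at all, and the document does not support that.
- The same incremental power test is performed before training starts.
- The sample-size section sizes the study for the pre-training gain, which suggests it was meant to be measured.
- The Statistical analyses section plans paired t tests of strength and power before and after interventions, in the plural, and the objectives call pre-training an intervention. A paired comparison across training fits that wording.
- Study limitations says the effect of pre-training cannot be judged on tissue and blood markers, and makes no such statement about muscle function.
- The primary outcome's second clause, on group differences, could mean day-15 levels. That reading would keep the gain.
- The text is a condensed article and its timeline figure was not available, so a further assessment may be marked there.

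All of this stands against the claim that the question is unanswerable. It does not remove the mismatch. The stated window is pre- to post-step-reduction, and none of these readings is specified. Comparing day-15 levels would not test whether PT stays above its own pre-training level, and leg power is not a minimisation factor.

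Two other inferences go too far. One is that a null PT result would be taken as failure: the plan says in advance that equal decline is expected. The other is that an adjustment for day-0 power would remove the gain: it would, but none is planned. The 5% figure likewise applies only if the change is tested between groups, and the article specifies only paired tests for power.

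**Conclusion.** The point holds as a mismatch between the primary outcome and hypothesis 2. On the plan's own assumption of equal decline, the expected PT-minus-control difference in the day 0 to day 15 change is 0 whatever the training gain, with about a 5% chance of significance if tested between groups. Counted from before training, the expected difference is the whole gain G, provided control is stable before day 0.

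Hypothesis 2 remains answerable from data the trial already generates, but the article does not name the comparison that would answer it. Because G in power and its SD are not given, the power of that comparison is unknown. The range shown runs from 5% (G equal to the loss) to over 99%. The problem concerns the PT-group only. It should be corrected, because following the stated outcome literally gives one of the two experimental arms an expected null between-group change.

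**What to change.** 1. Keep the day 0 to day 15 change in leg power as the primary outcome for hypothesis 1 (control) and hypothesis 3 (ES versus control).
2. Name the incremental power test at the second familiarisation session as the recorded pre-training baseline in all arms.
3. Test hypothesis 2 within PT as day-15 power minus that baseline.
4. Make PT versus control a comparison of day-15 power, adjusted for the pre-training value or expressed as change from it. Do not adjust this contrast for day-0 power.
5. Report the PT-group's day 0 to day 15 change as its rate of loss.
6. State the assumed gain in power and its SD, and the resulting power of the hypothesis 2 test.

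**Cost.** Outcome and analysis wording, plus keeping the values from a test already performed. Recruitment is ongoing, so values from participants already past familiarisation should be secured now.

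**Downside.** A familiarisation value is noisier than a main-trial value and carries a learning effect. Between familiarisation and day 0 the PT-group also has 10 sessions on the same leg press and an extra power test at session five, with no comparable practice described for the other groups. Part of its apparent gain may therefore be learning, and the report should say so.
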